## Abstract

**Background:**

Cataract surgery has become one of the most performed surgical procedures worldwide. Postoperative management consists of routine clinical examinations to assess post-operative visual function and detect possible adverse events. Due to the low incidence of complications, the majority of clinic visits after cataract surgery are uneventful. Nonetheless, valuable time and hospital resources are consumed. We hypothesize that remote post-operative follow-up involving teleconsultations and self-assessments of visual function and health status, could be a valid alternative to face-to-face clinical examinations in selected patient groups. The practice of remote follow-up after cataract surgery has not yet been evaluated. The aim of this study is to investigate the validity, safety and cost-effectiveness of remote cataract surgery follow-up, and to report on the patients’ experiences with remotely self-assessing visual function.

**Methods:**

This study is a multicenter, open-label, randomized controlled trial. Patients planned for cataract surgery on both eyes, without ocular comorbidities, are eligible for participation. Participants will be allocated (1:1) into one of the two study groups: ‘telemonitoring’ or ‘usual care’. Participants in the ‘telemonitoring’ group will perform in-home assessments after cataract surgery (remote web-based eye exams and digital questionnaires on their own devices). Participants in the ‘usual care’ group will have regular post-operative consultations, according to the study site’s regular practice. Outcome measures include accuracy of the web-based eye exam for assessing visual acuity and refraction, patient-reported outcome measures (visual function and quality of life), adverse events, and cost aspects.

**Discussion:**

Investigating remote follow-up after cataract surgery fits the current trends of digitization of health care. We believe that remote self-care can be a promising avenue to comply with the increasing demands of cataract care. This randomized controlled trial provides scientific evidence on this unmet need and delivers the desired insights on (cost)effectiveness of remote follow-up after cataract surgery.

**Trial registration:**

ClinicalTrials.gov: NCT04809402. Date of registration: March 22, 2021.

**Supplementary Information:**

The online version contains supplementary material available at 10.1186/s12886-023-02779-7.

## Background

Cataract, clouding of the eye’s natural lens, is one of the leading causes of blindness and visual impairment worldwide [1, 2]. It is most commonly age-related, and therefore a common condition amongst older-aged adults [2]. The main treatment is surgical extraction of the cataract, followed by implantation of a clear artificial lens [3]. Across the European Union member states, cataract surgery is conducted 4.3 million times yearly, making it the most performed surgical procedure [4]. Due to increasing life expectancies and aging of the population, these numbers are expected to keep increasing.

Over the last decades, new technologies and surgical techniques have revolutionized the procedure, making cataract extraction one of the safest surgeries to be performed [2, 5]. Based on the latest report of the European Registry of Quality Outcomes for Cataract and Refractive Surgery (EUREQUO), 98% of the procedures remained uneventful [6]. Infectious endophthalmitis, the most dreaded short-term post-operative complication with a devastating prognosis, only occurred in 0.01% of the cases [6]. Other short-term post-operative consultations include cystoid macular edema (0.46%), persistent corneal edema (0.02%), and uncontrolled elevated intraocular pressure (0.02%) [6].

Cataract surgery is usually performed in day care. A recent innovation is immediate sequential bilateral cataract surgery, further improving the cost-effectiveness of cataract care as both eyes will be operated on the same day [7]. Typical postoperative follow-up consists of a short-term evaluation within a few days after surgery and a long-term evaluation approximately 1 month after surgery [8]. The main purpose of the short-term postoperative consultation is to ascertain no complications have occurred immediately after surgery, such as an elevated intraocular pressure [9–12]. At approximately 1 month after surgery, the residual refractive error is determined and routine postoperative cataract care is finished. Due to the low rate of (serious) adverse events, the majority of postoperative examinations after cataract surgery will be uneventful [5–14]. Nevertheless, because of the high number of cataract surgeries performed, postoperative follow-up of cataract patients takes up a considerable amount of hospital time and resources. To maximize the efficiency of postoperative cataract care, the clinical examination shortly after surgery is often replaced by a telephone consultation [15]. Notwithstanding, telephone consultations lack quantifiable outcome parameters.

Remote follow-up could be a cost-effective and patient friendly alternative to conventional in-hospital follow-up. A remote monitoring platform that includes assessments of visual function using e-health technology could enable patients to self-monitor their postoperative eye status and remotely provide quantifiable outcome parameters, such as visual acuity, to their eye care professional.

An e-health tool that can be used for this purpose has been developed by the Amsterdam-based medtech company Easee (https://easee.online). It allows users to self-assess their visual acuity and refractive error via a website, using their own electronic devices (a computer or tablet, and a smartphone). Previous research indicated the refraction assessment of this tool to be non-inferior to a manifest refraction performed by an eye care professional, investigated amongst healthy volunteers with refractive errors, achieving the best outcomes in low myopes [16]. Moreover, studies have shown that visual acuity can be reliably assessed in patients with various ocular conditions [16–18]. Most studies have been targeting relatively younger-aged individuals and we suspect that introducing e-health technology to older-aged generations will be more challenging. Interestingly, a recent study on the performance of the remote assessment in post-operative cataract patients identified that the majority of patients were able to complete the assessment and achieve accurate visual acuity scores [19]. This study was performed in a supervised, controlled setting and only evaluated distance visual acuity assessments. In the present study, the remote exam will be more comprehensive and also include refractive error assessments, as well as near vision. Moreover, examinations will be performed unsupervised by patients at home, using their own smartphones and computers, mimicking a future real-world application of this tool.

In summary, we hypothesize that remote follow-up could be a valid alternative to conventional face-to-face examinations in post-operative cataract care. This randomized controlled trial aims to investigate the validity, safety and cost-effectiveness of remote follow-up after cataract surgery, and provide insights on patients’ experiences with remotely assessing visual function.

## Methods

### Study design and setting

This study will assess the validity of a web-based eye exam, report on patients’ experiences with this tool, and evaluate the cost-effectiveness and safety of remote follow-up. Therefore, we will perform a randomized controlled trial to make a comparison between two different methods of post-operative follow-up: “telemonitoring” vs. “usual care”. The study is titled the CORE-RCT: Cataract Online Refraction Evaluation – a Randomized Controlled Trial. The protocol for this study was designed according to the SPIRIT 2013 guidelines [20].

Multiple centers will participate in the trial. The sponsor of this study is the University Medical Center Utrecht, the Netherlands. Participating centers are the Maastricht University Medical Center+, the Netherlands; Amphia Hospital Breda, the Netherlands; Oogcentrum Noordholland, the Netherlands; Vienna Institute for Research in Ocular Surgery, Austria; and Augenklinik Sulzbach, Germany. Each of the participating sites reviewed a copy of the research protocol and provided written approval and agreement to participate in this study. The study has been approved by the Medisch Ethische Toetsingscommissie Utrecht, the Netherlands (NL74625.041.21); the Ethikkommission der Stadt Wien, Austria (EK 20-334-0121); and the Ethikkommission Saarbrücken, Germany (Ha 44/18).

### Study objectives

This randomized controlled trial aims to evaluate remote follow-up after cataract surgery. The objectives of this trial can be categorized into four categories: validity, safety, cost-effectiveness, and patients’ experiences.

#### Validity of the web-based eye exam

Validity of the web-based eye exam (developed by Easee B.V.) will be assessed by comparing the web-based outcomes to the clinical findings at the visit scheduled 4-6 weeks after surgery. Our main objective will be to determine if the corrected distance visual acuity (CDVA) achieved with the refraction resulting from the remotely performed web-based refraction assessment is non-inferior to the achieved CDVA with the prescription of the in-hospital manifest refraction. A mean difference between the two scores up to 0.10 logMAR (one ETDRS line) will be considered clinically acceptable (i.e. non-inferior). In addition, we will assess uncorrected distance visual acuity (UDVA) and compare the outcomes of the web-based vs. the in-hospital assessment. Furthermore, we will evaluate the accuracy of the web-based exam for determining refractive error and uncorrected near visual acuity, by comparing these outcomes to the conventional in-hospital assessments. The repeatability of the web-based refractive assessment will be determined by comparing the outcomes 4-6 weeks after surgery to the outcomes 3 months after surgery (on the condition that post-operative complications resulting in a change of visual function are absent).

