### Study population and sample size calculation

Patients planned for bilateral cataract surgery without visual acuity influencing comorbidities are eligible for study participation. The surgical procedures can be performed on the same day (i.e. immediate sequential) or on two different days. Exclusion criteria are: cataract surgeries combined with other procedures (including keratoplasty, vitrectomy, glaucoma filter implants), presence of ocular comorbidities that negatively influence post-operative visual acuity (such as amblyopia, age-related macular degeneration, diabetic retinopathy, glaucoma or uveitis), insufficient command of the Dutch, German or English language, no access to a smartphone and computer/tablet, and inability to successfully perform the demo version of the web-based eye exam.

The sample size calculation is based on determining the validity of the web-based eye exam since calculations based on cost-effectiveness and safety were not feasible. We aim to assess whether the corrected distance visual acuity obtained with the web-based refraction is not significantly worse than the visual acuity obtained with the manifest refraction. We assume no difference between the measurements and consider a difference up to 0.10 logMAR to be non-inferior. With a standard deviation of 0.30 logMAR (a commonly used SD in power calculations on visual acuity [29–31]), an α of 0.05, a power of 90, 20% loss to follow-up and using a one-sided, one sample t-test, 94 eyes are then required in the telemonitoring group (so 47 participants, as all measurements will be performed bilaterally). This results in a total study population of 94 participants (188 eyes) for both study groups.

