#### Study measurements

The ‘telemonitoring’ group will have a post-operative follow-up involving web-based eye exams, digital questionnaires and telephone consultations. The invitations for the web-based eye exams and questionnaires will be sent via e-mail at 4 specific time points: prior to surgery, < 1 week after the surgery, 4-6 weeks after the surgery and 3 months after surgery. Prior to surgery, visual acuity will be assessed with the participant’s current spectacles, if applicable. After surgery, the web-based eye exam will be performed without spectacles. In addition, participants will fill out triage questionnaires to identify any (alarming) symptoms.

Shortly (1-7 days) after surgery, uncorrected distance visual acuity (UDVA) will be assessed remotely, and a telephone consultation will take place if deemed necessary by the surgeon. Approximately 1 month (i.e. 4-6 weeks) after surgery, the web-based tool will assess uncorrected visual acuity (distance and near) and the residual refractive error. After performing this remote assessment at home, participants will have an in-hospital ophthalmic examination with conventional visual acuity and refraction assessments for validity and safety purposes. The observer and participant will be blinded for the web-based refraction outcome during the manifest refraction. At this in-hospital consultation, distance visual acuity will be assessed by an ETDRS chart at 4 m, both uncorrected (UDVA) and corrected (CDVA). The CDVA will be assessed twice: using both the prescriptions of the web-based and the manifest refraction. Near visual acuity will be assessed uncorrected using a Sloan ETDRS chart at 40 cm. Three months after surgery, the web-based assessment will be repeated and participants will be requested to fill out a questionnaire about their experiences with the web-based eye exam. In addition, a sample of the Dutch-speaking participants will be interviewed to further explore their perspective on remote follow-up after cataract surgery.

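### Assay sensitivity of the main validity test is not assured: the 0.10 logMAR margin is not tied to how much acuity correction gains in these eyes

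*Protocol article*

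**What the plan says.** Under the heading Validity of the web-based eye exam, the main objective is that CDVA with the web prescription "is non-inferior to the achieved CDVA with the prescription of the in-hospital manifest refraction". The decision rule follows: "A mean difference between the two scores up to 0.10 logMAR (one ETDRS line) will be considered clinically acceptable (i.e. non-inferior". The sample size section repeats the margin: "We assume no difference between the measurements and consider a difference up to 0.10 logMAR to be non-inferior". This is the only comparison on which the trial was sized.

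The population is described as follows: "Patients planned for bilateral cataract surgery without visual acuity influencing comorbidities are eligible for study participation". No minimum residual refractive error is required, and the article states no target refraction and no expected post-operative UDVA, CDVA or residual error.

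At the 4-6 week hospital visit, "distance visual acuity will be assessed by an ETDRS chart at 4 m, both uncorrected (UDVA) and corrected (CDVA", and CDVA is read once with each prescription. Hospital UDVA is therefore available on the same chart and at the same visit as both CDVA readings. The objectives use it only to check the web-based UDVA. Agreement on refractive error and repeatability of the web refraction are also planned, as additional analyses with no stated acceptance limit.

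**The concern.** A non-inferiority result is informative only if a useless intervention would have failed the same test. Here the useless intervention is easy to name: a tool that returns no correction for every eye. For that tool, CDVA with its prescription is simply UDVA, so the primary difference equals UDVA minus manifest CDVA.

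If the mean of that difference is below 0.10 logMAR, the blank tool is truly non-inferior by the plan's own criterion. The article defends the margin as one chart line and clinically acceptable. It does not show that the margin is smaller than the benefit of manifest refraction in these eyes, so nothing in it establishes that the test can separate a working tool from a blank one.

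Averaging adds to the problem. Eyes that need little correction can dilute a real loss in the minority that need more. What is at stake is the meaning of the trial's one powered conclusion, which is to support remote follow-up as a valid alternative to the hospital examination.

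**Working it through.** **Inputs from the sample size section.** Margin 0.10; true difference 0; "With a standard deviation of 0.30 logMAR"; "an α of 0.05, a power of 90, 20% loss to follow-up and using a one-sided, one sample t-test". Stated result: "94 eyes are then required in the telemonitoring group".

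**Reproducing the plan's figure.** n = (SD × (z0.95 + z0.90) / margin)² = (0.30 × 2.926 / 0.10)² = 77.07, so 78 evaluable eyes. Multiplying by 1.20 gives 93.6, rounded up to 94. The stated figure is reproduced, and 78 is used below as the planned evaluable number.

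**Assumed input.** Let d be the true mean of UDVA minus manifest CDVA. The documents do not give it, so a range is shown. Eyes are treated as independent, as in the protocol's own calculation.

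**Pass rule.** The one-sided 5% t-test against 0.10 passes if the observed mean is below 0.10 − t0.95,77 × SD/√78, with t0.95,77 = 1.665. This limit is 0.081 for SD 0.10, 0.072 for SD 0.15 and 0.043 for SD 0.30.

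**Probability that the blank tool passes.** This is 1 − F(1.665), where F is the noncentral t distribution with 77 degrees of freedom and noncentrality (0.10 − d)/(SD/√78). For d = 0.05 and SD 0.30 the noncentrality is 0.05/0.0340 = 1.47, which gives 43%.

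| d (assumed) | SD 0.10 (assumed) | SD 0.15 (assumed) | SD 0.30 (planned) |
|---|---|---|---|
| 0.02 | >99% | >99% | 75% |
| 0.05 | 99.7% | 90% | 43% |
| 0.06 | 97% | 75% | 32% |
| 0.08 | 54% | 32% | 14% |
| 0.10 | 5% | 5% | 5% |

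Above d = 0.10 the probability falls below 5%.

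**Sensitivity to the number of eyes.** With 75 eyes (94 less 20%), the d = 0.05 row becomes 99.6%, 89% and 42%. With an assumed fellow-eye correlation of 0.5, the effective number is 75/1.5 = 50 and the row becomes 97%, 75% and 31%. Fewer effective eyes lower the pass rate but do not remove the problem.

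**Dilution, on assumed figures.** Suppose 20% of eyes gain 0.25 logMAR from correction and 80% gain nothing. The mean gain is 0.20 × 0.25 = 0.05, and the SD, before measurement noise, is 0.25 × √(0.20 × 0.80) = 0.10. The blank tool would then pass almost always (99.7%), while every eye that needed correction was left 2.5 lines short.

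**Would a rule that web CDVA must beat UDVA in all eyes solve it?** Take a perfect tool whose CDVA equals manifest CDVA. Its chance of showing a gain over UDVA (78 eyes, one-sided 5%) has noncentrality d/(SD/√78). At SD 0.30 this gives 43% for d = 0.05 and 14% for d = 0.02. At d = 0.02 it is 32% for SD 0.15 and 54% for SD 0.10. Such a rule would often reject an accurate tool merely because the eyes need little correction.

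**The case against.** A reader might infer that the endpoint has no assay sensitivity at all, and that the trial would succeed whether or not the tool measures refraction. The documents do not support that.

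- **The gain is unknown.** The article speaks of residual refractive error but does not say that it is small, and target refraction is not restricted. If d is 0.10 or more, the blank tool fails at least 95% of the time.
- **The highest pass rates use SDs that are not in the protocol.** At the planned SD of 0.30 the blank tool fails more often than it passes for d of 0.05 or above.
- **Wrong, non-zero prescriptions can worsen CDVA and fail.** The endpoint still detects harmful error. The weakness concerns outputs close to zero.
- **Other checks are planned.** Refractive error is compared by Bland-Altman methods, repeatability is assessed, and associations between clinical characteristics and agreement are examined. Summaries of all quantitative variables would show UDVA and both CDVA readings.
- **The consequence is not immediate.** The Discussion foresees revising the algorithm and a further study stage. An acuity loss of less than one line in the intended population is also a legitimate clinical question.

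These points remove the categorical claim but leave the conditional one. The planned agreement analyses have no acceptance limit and do not govern the main conclusion. Repeatability offers no protection here, because a constant blank output is perfectly repeatable. The missing link is in the stated decision rule itself, not in detail that an article would leave to an analysis plan.

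**Conclusion.** The concern stands in conditional form. Meeting the 0.10 logMAR margin does not by itself show that the web refraction works, because the margin is not related to the gain from manifest correction in these eyes. How much this matters depends on an unstated quantity: it is serious if the mean gain is about 0.05 logMAR or less and the paired SD is 0.10-0.15, moderate at the planned SD, and absent in practice once the gain reaches 0.10. These figures rest on an assumed gain, on assumed SDs other than 0.30, and on eyes treated as independent. The sample size itself is not in question on this point.

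**What to change.** 1. Use same-visit hospital UDVA as the no-correction benchmark. Beside the main result, report UDVA minus manifest CDVA and UDVA minus web CDVA, each with a confidence interval. State in advance that, if the mean gain from manifest correction is below the margin, CDVA non-inferiority alone will not be taken as evidence that the web refraction is valid, and the conclusion will rest on the planned refractive-error agreement.
2. Pre-specify the same non-inferiority estimate in eyes whose manifest refractive error exceeds a threshold that the sponsor sets beforehand. Limit any claim about eyes needing correction to that result.
3. Do not make superiority of web CDVA over UDVA in all eyes a condition of success, for the reason shown in the working.

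The cost is protocol and analysis-plan wording plus a few paired analyses. No new measurement, visit or patient is needed. The downside is that the subset will be smaller and less precise, and the eventual claim may be narrower.

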#### Safety of remote follow-up

Safety will be evaluated by reporting on the occurrence of (serious) adverse events in both groups. Furthermore we will evaluate to what extent the digital triage questionnaires can detect alarming symptoms and adverse events.

#### Cost-effectiveness of remote follow-up

The cost-effectiveness will be evaluated by quality-adjusted life years (QALYs), total costs (societal and hospital costs), and the probability of adverse events or additional clinical examinations. The main outcome measure will be incremental cost-effectiveness ratio (ICER), defined as euros per QALY (based on the EQ5D-5 L questionnaire [21]), and compared between the two study groups.

#### Patients’ perspective

Firstly, we will determine if remotely self-assessing vision influences patient-reported outcome measures of visual function (Catquest-9SF and NEI-VFQ-25 questionnaires [22, 23]) and quality of life (EQ-5D-5L questionnaire [24]), by comparing the outcomes between both randomization groups.

Secondly, we will evaluate the user experiences with the web-based tool by a custom quantitative questionnaire, distributed amongst the participants of the telemonitoring group at the end of the study. This questionnaire is based on the theoretical Technology Acceptance Model; a commonly used model to evaluate and incorporate user experiences in the development process of technology. Since its introduction by Davis in 1989 [25], the model has been extended by multiple research teams, including for utilization in health care settings [26–28]. We used the extended models as a reference framework and developed a study-specific questionnaire in cooperation with the University of Twente, the Netherlands (Additional file 1). Lastly, the quantitative results are enriched with in-depth qualitative interviews (Additional file 2). Dutch-speaking participants of the telemonitoring group will be invited to report on their experiences with the web-based eye exam. Interviews will be conducted by researchers experienced in qualitative interview studies, until data saturation is reached (i.e. when no longer new insights are gained).

